### Comparison group

Participants will serve as their own controls. Pre- and post-treatment results will be compared to inform a future power calculation.

### Measures

Apart from the measures that participants and their caregivers fill out at home [SCAS, SMFQ, demographics], all other measures and assessments will be conducted in the CAH-Y facilities.

### Socio-demographic characteristics and psychiatric conditions

Primary caregivers will provide socio-demographic information. The PI will acquire psychiatric/medical information, via the participant’s digital medical records. Axis-1 diagnoses are given during ordinary clinical practice by the youth’s psychiatrist or psychologist after reaching a consensus with other professionals from the multi-disciplinary team. In this study, we will classify the patients according to their main Axis I psychiatric diagnoses (ICD-10 codes are specified in Table 2) in the following groups: *depressive disorders*, *anxiety disorders*, *hyperkinetic disorders*, *pervasive developmental disorders,* and *other disorders* (a broad spectrum of psychiatric disorders with low frequency). The assessment and diagnosis of youth in CAMHS will provide the necessary information in order to asses study eligibility according to the predetermined inclusion/exclusion criteria.

### Feasibility outcomes

Feasibility of the trial will be done by way of continuous tracking of participant recruitment (number of youth referred/number of the youth assessed as eligible), attendance, and retention. The appropriateness, practicality, and acceptability of the intervention within the CAMHS setting, will be explored through feedback from participants, primary caregivers, and the referring specialists. This information will be gathered via semi-structured qualitative interviews, during the pre- and post-treatment assessment, while the referring specialists will be interviewed separately following the post-treatment assessment. Furthermore, the researchers will meet with the steering group at the end of the study to discuss the results and intervention acceptability.

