### Study population and eligibility

Youth are referred to the treatment program from their attending therapist at the local CAMHS. Youth can be included in the study if they meet the criteria below.

Inclusion criteria are as follows:Age 8–17 yearsSymptoms of anxiety and/or depressionYouth display reduced daily physical activity (less than 30 mins per day and/or does not partake in physical leisure activities, and/or does not participate in physical education in school).The youth is motivated to partake in physical activity

Exclusion criteria are as follows:Physical activity is not advised for medical reasonsSevere learning disabilities and the youth is unable to understand the study protocolSpecific psychiatric disorders including any eating disorder, psychosisSevere challenging behavior or other needs requiring constant one to one support

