### Recruitment

Youth will be recruited from the CAMHS, Department of Child and Adolescent Psychiatry, Haukeland University Hospital, Norway. CAMHS is organized at the same intervention level as ordinary hospital services (Haukeland University Hospital, Bergen, Norway) and is as such a tertiary specialized service. In the Norwegian context, this is the primary source of treatment for youth with mental health disorders. CAMHS is organized in three inpatient wards, three specialized clinics, and seven outpatient clinics. These units together form the recruitment base for CAH-Y. CAMHS offers all forms of mental health services to youth in a catchment area of app. 460,000 citizens in total. The CAMHS receives approximately 3000 referrals per year and delivers treatment to 5.2% of all youth in the catchment area [37]. Taking into account CAH-Y inclusion and exclusion criteria, we estimate that 40% of these youth qualify for participation in the intervention (*n* = 600). The likely numbers of patients referred and eligible should greatly exceed the numbers required by the feasibility study, meaning well below 10% of those eligible are required to consent.

Given that CAH-Y is organized within CAMHS, this enables easy access to potential participants and streamlined recruitment strategies. In practice, this translates into the following:Uncomplicated dispersion of information regarding the intervention to the departments and mental health professionals via intranet, email and/or physical/digital meetingsEase of implementing an in-house digital referral systemA low threshold for communication between the CAH-Y team and the referring specialist

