Based on the therapist’s assessment of eligibility and participant’s interest in the intervention, the therapist sends a formal referral to the CAH-Y team. The referrals are assessed with respect to inclusion/exclusion criteria by the Principal Investigator (PI is the first author). If the youth is assessed eligible, an invitation to attend a recruitment and inclusion interview is sent to the youth (and parents if the youth is below 16 years of age). Enclosed in the letter are also a number of health assessment questionnaires. The questionnaires assess mood, anxiety, demographic information, and motivation to attend the intervention. Finally, this letter informs of a webpage address, where the participant can find more information about the intervention and the study. The referring specialist will receive notification that the youth is eligible and is invited to an interview. Approximately a week prior to the interview, youth/parents are contacted via phone and they are given further information about the intervention and study participation.

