### Progression criteria

A feasibility study is not adequately powered to test the any hypothesis (e.g., the efficacy of CAH-Y physical activity intervention) but is intended to improve the chances of conducting a high-quality RCT. Therefore, in line with suggestions by el-Kotob et al. [46], a priori criteria for progression to the definitive large-scale RCT are advisable. The progression criteria to move on to a definitive large-scale RCT will be as follows: (A) no serious adverse events, such as hospitalization, a life-threatening condition, death, and any adverse events associated with the intervention; (B) recruitment rate of no less than 75%; and (C) retention rate of no less than 60% in each group at 7 weeks (total of 14 sessions). If all the three criteria are not met, we assess there is insufficient evidence to justify proceeding to the definitive RCT. Consequently, changes to the intervention would then be required with consequent re-runs of the intervention following, up until these criteria are met.

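### Read as written, the recruitment ratio is never below 100%, so a 75% progression floor that uses it could not fail, and no reading of it counts consent

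*Protocol article*

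**What the plan says.** Under Feasibility outcomes, the article says that feasibility will be judged by "continuous tracking of participant recruitment (number of youth referred/number of the youth assessed as eligible), attendance, and retention". This is the only place where it says what recruitment is measured by.

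Under Progression criteria, the second of three conditions for moving to the definitive RCT is a "recruitment rate of no less than 75" per cent. That section gives no numerator or denominator and does not refer back to Feasibility outcomes. A shortfall leads to changes to the intervention and re-runs.

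The Recruitment section sets the order of events. The therapist first judges eligibility; then, given the youth's "interest in the intervention, the therapist sends a formal referral to the CAH-Y team". Next, "The referrals are assessed with respect to inclusion/exclusion criteria by the Principal Investigator". Those found eligible are invited to the inclusion interview. Under Consent, written study consent is obtained at that interview, and a youth may take part in the intervention without joining the study.

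The first principal aim, listed before Methods and design, is to quantify recruitment rate and willingness to participate, among other things.

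**The concern.** A recruitment rate normally has those who agree to take part in the numerator and those who could have agreed in the denominator. Here the larger group (referred) stands over a smaller group drawn from it (eligible), and those who agree appear in neither term. A floor of 75% on a quantity that starts at 100% is no test. The ratio also moves the wrong way, because it rises as more referrals turn out to be ineligible.

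At stake is one of the three gates to the RCT. If most invited youth declined the study, criterion B could still be reported as met. The decision to proceed would then rest on a figure that says nothing about whether families will consent.

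**Working it through.** **Inputs**
- R = youth referred, and E = youth assessed as eligible (Feasibility outcomes; Recruitment).
- E is counted among R, because the principal investigator applies the criteria to the referrals (Recruitment). Hence E ≤ R.
- C = youth with written study consent, obtained after eligibility is decided (Consent). Hence C ≤ E.
- Floor for criterion B: 75% (Progression criteria). The article gives no derivation for it, so there is no figure to reproduce.
- Target sample: 20 (Sample size).

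**Step 1. Range of the stated ratio.** Since E ≤ R, R/E ≥ 1. Enumerating every R from 1 to 300 with every E from 1 to R gives a minimum of 1.00, reached when every referral is eligible. The floor of 0.75 lies below the whole range.

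**Step 2. What the ratio misses.** The article reports no counts, so those below are assumed, for illustration only.

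| R | E | C | R/E (as stated) | E/R (inverted) | C/E (consent) |
|---|---|---|---|---|---|
| 40 | 30 | 20 | 133% | 75.0% | 66.7% |
| 40 | 30 | 6 | 133% | 75.0% | 20.0% |
| 60 | 40 | 20 | 150% | 66.7% | 50.0% |
| 100 | 80 | 20 | 125% | 80.0% | 25.0% |

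R/E clears 75% in every row, and C/E clears it in none. Rows one and two differ only in consent, and R/E does not change between them.

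**Step 3. The other readings of the slash.**
- Inverted, E/R: this can fall below 75% (row three), but it measures how well referrals match the criteria. Consent is still absent.
- A list of two tracked counts: criterion B then has no defined numerator or denominator.

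**Step 4. What 75% means once consent is counted.** For C = 20, C/E ≥ 0.75 requires E ≤ 20/0.75 = 26.7, so at most 26 invited. 20/26 = 76.9% passes and 20/27 = 74.1% fails.

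Wilson 95% interval for 20/26, with p = 0.769, n = 26 and z = 1.96:
- Centre: (p + z²/2n)/(1 + z²/n) = (0.7692 + 0.0739)/1.1478 = 0.735.
- Half-width: z·√(p(1−p)/n + z²/4n²)/(1 + z²/n) = 1.96 × √(0.00683 + 0.00142)/1.1478 = 0.155.
- Interval: about 58% to 89%. The exact interval is 56.4% to 91.0%.

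**The case against.** The strongest reply is that applying this definition to criterion B is an inference. Progression criteria does not cite Feasibility outcomes, and the sentence in Feasibility outcomes speaks of tracking and never calls the quantity a rate. The article elsewhere uses a slash to join items, as with inclusion and exclusion criteria, so the parenthesis may name two counts, or a ratio may have been transposed. This stands as a limit on how firmly one can say that B passes automatically. It does not rescue B, which is then undefined or blind to consent.

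A second reply is that therapists also judge eligibility before referring. If that judgement were the denominator, the ratio would be at most 100% and would reflect early interest. However, the Recruitment section uses the wording of being assessed eligible for the step that leads to the invitation, so the principal investigator's step is the more natural denominator. Study consent is missing on this reading too.

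A third reply is that the first aim lists recruitment rate and willingness separately, and that "The youth is motivated to partake in physical activity" is a declared inclusion criterion. That is fair. Restricting the study to interested and motivated youth is a design choice, not an error. It does mean that any rate computed here applies only to youth who have already passed that filter.

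A reader might also infer from "meaning well below 10% of those eligible are required to consent" that recruitment means consent among the whole estimated eligible pool, which would put 75% out of reach. The documents do not support this. That sentence argues that the pool is large enough; it neither defines a recruitment rate nor connects one to the 75% floor.

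**Conclusion.** The concern holds in a conditional form. The only stated measure of recruitment, read as a quotient with eligibility assessed among the referrals, cannot be below 100%, so criterion B could not fail if it uses that measure. If it does not, B is either undefined or a measure of referral accuracy. The omission of consent does not depend on which reading is right.

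A reader might go further and say that the plan guarantees a pass. The documents do not establish that, because the article never ties the criterion to the definition.

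The size of the distortion in this trial cannot be given, because no referral, eligibility or consent counts are reported. The illustrative counts show stated ratios of 125% to 150% alongside consent of 20% to 66.7%. The matter should be corrected, because it governs one of three gates to the RCT and is a stated definition and threshold that do not work together, not a detail left to a fuller document.

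**What to change.** - In Feasibility outcomes and Progression criteria, define the recruitment rate as youth with written study consent divided by youth referred, assessed eligible and invited to the inclusion interview.
- Have the sponsor confirm that 75% is still the intended floor for this denominator, knowing that 20 consents meet it only with at most 26 invited and that the interval around such a result is wide.
- Report eligible/referred separately, labelled as referral accuracy.
- Report intervention uptake among those invited separately. Youth may enter the programme without study consent, and the consent rate alone would count them as refusals.
- State that the definition was set while recruitment was under way, since inclusion began in April 2020.

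The cost is a change of wording in two sections. The invitation and consent procedures already generate the counts, so no new data are needed from participants. The downside is that the reported rate will never exceed the present ratio and will usually be lower, and criterion B can now fail. The change does not capture youth who declined before referral, so the rate should be described as applying to referred youth only.

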### Participant-centered outcome measures

*Objective measures of physical activity* will be collected using the wearable activity sensor Actigraph GT3X+ monitor. The sensor captures and records continuous, high-resolution physical activity, and sleep/wake information and can record daily time spent in sedentary, light, and moderate to vigorous physical activity (MVPA). Other research has documented this method to be valid and reliable [38]. Pre-defined minimum wear time for a valid day will be defined as 6 h per day with a minimum of 3 days of data required for analysis inclusion [39]. Data for the Actigraph will be downloaded using Actigraph Actilife software and interpreted using 30-s epochs and the following cut-off points: sedentary (<100 cpm) and MVPA (≥3200cpm) [40]. Non-wear time will be defined as 60 min of consecutive zero counts. Participants will also be asked to wear the Actigraph during each intervention session to provide data on physical activity and MVPA content of the sessions.

Participant *height* will be measured in meters and rounded to the nearest 0.1 cm. *Weight* will be measured in kilograms and rounded to the nearest 0.1kg.

*Anxiety symptoms* will be assessed using Spence Child Anxiety Scale, child, and parent version (SCAS-C/P) (Spence, 1998). The SCAS comprises 38 items rated on a 4-point scale (0 = never, 1 = sometimes, 2 = often, 3 = always), with a maximum score of 114. SCAS-C/P has demonstrated good psychometric qualities [41].

*Affective symptoms* will be assessed using Short Mood and Feelings Questionnaire, and child and parent version (SMFQ-C/P) (Angold, Costello, Messer, & Pickles, 1995) is used to assess youth affective symptoms. The SMFQ has demonstrated good psychometric qualities [42].

*Intervention motivation* will be assessed using Nijmegen Motivation List Child (NML-C) [43]. This is used widely to assess treatment motivation in children and adolescents. The NML-C comprises 15 items rated on a 3-point scale.

The semi-structured qualitative interview will apart from feasibility outcomes also assess participant perceptions on PA in general, participant views on the association between PA and mental health, perceptions on the intervention components and the intervention as a whole, views on potential barriers to physical activity, motivation for activity, and participation in school-based physical activity. These questions will be posed at post-treatment and long-term follow-up. Caregivers will be posed the same questions; however, caregivers of youth aged 12 years or above will only receive these questions if the youth has consented to this. Answers to the questions are written down during the interviews and will be analyzed by thematic analysis [44]. An interview with the referring specialist, following the post-treatment interview with the participant, will similarly explore his/her experiences of the intervention including acceptability of procedures, perceived benefits, and difficulties.

An effect-size will be calculated for youth and caregiver reported depression and anxiety symptoms and activity level. Means (*M*) and standard deviations (*SD*) will be used to investigate the effect sizes for change between pre- to post-treatment. These results will help inform the power calculation of the likely required sample size for a future large-scale RCT.

### Timing

Measures will be assessed at baseline (pre-intervention interview) and at the latest 2 weeks after completing the intervention. Follow-up outcome will be assessed 6 months post-intervention.

### Sample size

As this will be the feasibility study to inform the design of the future definitive RCT, a target sample of 20 youth participants will be recruited for a mixed-methods assessment of feasibility [45].

### Progression criteria

A feasibility study is not adequately powered to test the any hypothesis (e.g., the efficacy of CAH-Y physical activity intervention) but is intended to improve the chances of conducting a high-quality RCT. Therefore, in line with suggestions by el-Kotob et al. [46], a priori criteria for progression to the definitive large-scale RCT are advisable. The progression criteria to move on to a definitive large-scale RCT will be as follows: (A) no serious adverse events, such as hospitalization, a life-threatening condition, death, and any adverse events associated with the intervention; (B) recruitment rate of no less than 75%; and (C) retention rate of no less than 60% in each group at 7 weeks (total of 14 sessions). If all the three criteria are not met, we assess there is insufficient evidence to justify proceeding to the definitive RCT. Consequently, changes to the intervention would then be required with consequent re-runs of the intervention following, up until these criteria are met.

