Specifically during the introduction and warm-up, the therapists give psychoeducation to the youth regarding the bidirectional interplay between thoughts, feelings, actions, and particularly the role of avoidance and alternative coping strategies. The exercises are designed to stimulate some distress, fear, and/or discomfort, and the therapists couple these feelings and reactions to the introductory psychoeducation and use the exercises as exposure therapy. A supportive and mastery motivational climate facilitates the individuals need for relatedness [25] and a safe space to practice exposure (being observed), provides an optimal environment to help the youth address, and overcome this fear [34]. Thus, the group format allows youth to observe other youth, allowing them to observe that other youth have similar feelings, fears, reactions, behaviors, and responses as themselves, e.g., we sweat when we are physically active, trying out new activities may make us feel anxious but can be done nonetheless. Gaining this knowledge can help normalize the youth’s understanding of both themselves and others. Importantly, group and peer support are identified as an important intervention component to support active lifestyles [35, 36].

In accordance with self-determination theory, the sessions also strive to satisfy the youths’ needs for autonomy (e.g., giving them choices within a menu of activities to do), competence (e.g., adapting exercises to meet the needs/fitness levels of students), and relatedness (e.g., focusing on group cohesion, group cooperation). Importantly in this regard, the sessions do not have a competitive focus, but focus on being supportive, enjoyable, and fun. An overview of the CAH-Y intervention is presented in Table 2.

**Table 2 Tab2:** Description of the intended structure and format of Confident, Active and Happy Youth program. Notes: *Pa* physical activity

Introduction Sessions 1–2	Treatment stage Sessions 3–12	Closing and transitioning Sessions 13–14
**Main theme:** Alliance and motivation Feeling secure in the group Alliance to the group/therapist Motivation to partake	**Main theme:** Challenge and exposure Moderate to vigorous PA From avoidance to exposure Strengthening motivation	**Main theme:** Transitioning to daily life Active “lifestyle” Continue exposure to PA Motivation to continue
Week 1 2 sessions of 50 min	Week 2-6 10 sessions of 50 min 2 sessions weekly	Week 7 1 session of 50 min 1 session of 3

*PA* Physical activity

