### Withdrawal of the study participants

At any time, participants can withdraw consent with no consequences for further intervention participation or other eventual benefits. If there are any serious adverse events, e.g., injury from the activities, details will be recorded and reported to the PI and to the work management group. CAMHS has appropriate insurance of the participants, if any adverse event should take place. In the case of adverse psychiatric effects are uncovered, this will be reported immediately to the participants referring specialist in CAMHS.

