### Possible harms

Potential harms of being involved in the intervention, and the assessments will be explicitly outlined in the participant explanatory statements and consent form. During assessment, the primary potential risk for participants may be to experience some psychological distress; however, this is not anticipated to exceed levels of psychological distress experienced previously in CAMHS or in their daily lives. During the intervention, the youth are expected to engage in physical activity with varying degrees of activity intensity. During such activities, the youth could potentially injure themselves or others physically, and/or they could experience some physio-psychological distress. All activities required in the intervention are preplanned and will be completed so as be to be as safe as possible, yet any movement (in a group) does necessarily entail some risk of injury. All accidents and injuries will be recorded and reported to the PI and the work management group. In addition, any adverse events or mental states observed among the participants (e.g., significant symptom deterioration, suicidal ideation or suicide attempt, reported or observed abuse and/or self-harm, excessive weight loss) will be monitored routinely throughout the study. Any such adverse events will be immediately reported back to the youth’s referring specialist, who is responsible for the youth’s mental health care. All study therapists and interviewers are experienced in working with youth with anxiety and depression and in responding to distress.

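### Progression criterion A sets no severity threshold for intervention-related adverse events, so read literally one minor related injury fails it and triggers a change and re-run

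*Protocol article*

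**What the plan says.** The Protocol article, Progression criteria, sets three conditions for going on to the definitive RCT. Criterion A is "no serious adverse events, such as hospitalization, a life-threatening condition, death, and any adverse events associated with the intervention". B and C are floors of 75% for recruitment and 60% for retention in each group. On failure the section says: "If all the three criteria are not met, we assess there is insufficient evidence to justify proceeding to the definitive RCT". It adds that "changes to the intervention would then be required with consequent re-runs of the intervention following, up until these criteria are met".

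Three other sections bear on how A would be applied:

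- Possible harms accepts that activities are planned to be safe, "yet any movement (in a group) does necessarily entail some risk of injury", and says that all accidents and injuries will be recorded and reported.
- Withdrawal of the study participants reads: "If there are any serious adverse events, e.g., injury from the activities, details will be recorded".
- Sample size states that "a target sample of 20 youth participants will be recruited for a mixed-methods assessment of feasibility". The intervention section gives each participant 14 sessions.

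**The concern.** Criterion A demands zero of something that the protocol itself says cannot be excluded. It begins as a rule about serious events, but its final item covers related events of every grade.

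The criterion is one of three that decide whether a definitive trial follows. Applied literally, a graze or a mild sprain would formally require a possibly sound programme to be changed and run again. Applied loosely, by passing over minor events when they occur, the criterion is no longer fixed in advance. Either way it does not separate a real safety signal from minor injuries to be expected in a group exercise programme.

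**Working it through.** The protocol gives no event rate and no operating characteristic for criterion A, so there is no stated figure to reproduce. The check is first of wording, then of size.

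**Wording**

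1. The last item of A can be read in two ways. It is either a further example of a serious event, or a second kind of event that must not occur. On the first reading a minor related event is called serious. On the second it is not called serious but is still forbidden. On both, one related event of any severity fails A.
2. No other section narrows it. The withdrawal section uses injury from the activities to illustrate a serious event and sets no severity limit, which supports the broad reading. Possible harms has every injury recorded, so a minor one would be known.
3. The failure sentence could literally mean failing all three criteria. The conjunction joining A, B and C, and the instruction to repeat until the criteria are met, show that each is required. Failing A alone is therefore enough.
4. Relatedness is ambiguous. The words about association with the intervention may qualify only the last item or the whole list. On the narrow reading an unrelated hospitalization counts; on the wide reading it does not. The text does not settle this.

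**Size (illustration only)**

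Inputs from the protocol: n = 20 (Sample size) and 14 sessions each (Intervention), so 20 x 14 = 280 person-sessions at full attendance. The related-event rate r per person-session is assumed, as is independence between person-sessions. As a sensitivity check, 60% attendance is also assumed, giving 0.6 x 280 = 168 person-sessions. This attendance figure is not the retention threshold in criterion C.

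P(fail A) = 1 - (1 - r)^N

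| Assumed r | N = 280 | N = 168 |
|---|---|---|
| 0.1% | 24.4% | 15.5% |
| 0.5% | 75.4% | 56.9% |
| 1% | 94.0% | 81.5% |

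On the participant scale, P(fail A) = 1 - (1 - p)^20, where p is the risk that a participant has at least one qualifying event:

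- An even chance of failing corresponds to p = 1 - 0.5^(1/20) = 3.4%.
- A 90% chance of passing needs p no higher than 1 - 0.9^(1/20) = 0.53%.
- If only serious and related events counted, with an assumed p of 0.5% to 1%, P(fail A) would be 9.5% to 18.2%.

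**What a pass would show**

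With 0 events in 20, the one-sided 95% upper limit is 1 - 0.05^(1/20) = 13.9%. A pass is therefore weak evidence about safety. This does not make the criterion too strict; it is a separate limit on what the result can carry.

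**The case against.** A strict safety gate for minors in a small uncontrolled first test is a defensible choice. Failing it leads to a revised programme and another run, not to abandonment. Both points stand, and they limit the consequence to delay and repetition.

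Three stronger inferences are tempting, and the documents do not support them.

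- *That A is close to unattainable.* Every event rate above is assumed. At 0.1% per person-session, A is passed about 76% of the time (84.5% with 168 person-sessions).
- *That hospitalization from any cause fails A.* This is one reading only. The prescribed remedy, changing the intervention, makes most sense for related events, which favours the wider reach of the relatedness phrase. The Recruitment section does say that "CAMHS is organized in three inpatient wards, three specialized clinics, and seven outpatient clinics", and these units form the recruitment base, but it gives no admission rate. The eligibility criteria exclude psychosis, any eating disorder and needs for constant one-to-one support.
- *That intended exposure distress fails A.* The intervention section says: "The exercises are designed to stimulate some distress, fear, and/or discomfort". No section calls that distress an adverse event.

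It can also be argued that Possible harms handles accidents and injuries in one sentence and adverse events in another, so a minor sprain may not be an adverse event at all. The withdrawal section points the other way by listing injury under serious adverse events. The sections therefore disagree, and that disagreement has to be resolved before A can be applied.

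Finally, Trial status reports that inclusion began in April 2020 and was still in progress, so rewording a pre-specified gate now carries its own risk. That stands and shapes the fix.

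**Conclusion.** The point holds as a badly worded decision rule that the article itself fixes, not as detail left to another document. Criterion A has zero tolerance and no severity threshold for related events. It sits badly with the sections on possible harms and withdrawal, and it leaves open whether its most severe items must be related to the intervention. That one minor related event is enough follows from the text and rests on no assumed rate, provided that a minor injury counts as an adverse event, which the withdrawal section implies.

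The size is not known. The 24%, 75% and 94% figures depend on assumed rates of 0.1%, 0.5% and 1% per person-session, full attendance and independence. They show that the outcome of the gate could turn on minor events, not that it will. The consequence is a required change and re-run.

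**What to change.** Reconcile Progression criteria, Withdrawal of the study participants and Possible harms:

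- Take the item on any related adverse event out of the serious-event list. Let A rest on events that meet a stated seriousness definition and are judged at least possibly related to the intervention. The definition is for the investigators to state; the withdrawal section's injury example must then agree with it.
- Have the existing steering committee judge relatedness, under a written rule fixed before event data are reviewed.
- Report non-serious related events descriptively, as a rate per person-session with a 95% CI.
- State beside the decision that 0/20 excludes only a risk above 13.9% (one-sided 95%).

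The drafting cost is a few sentences. The real cost is that judgement enters criterion A, exercised by a committee that also helped choose the components of the intervention. Because inclusion is under way, the change must be dated and disclosed, with a statement of whether any events were already known when it was made.
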